**Methods:**

The aim of this feasibility study is to inform the development of a definitive trial, focussing on the acceptability, safety of the intervention, feasibility of recruitment, adherence and tolerability to tDCS and study assessments and the size of the treatment effect. To this end, we will deliver a double-blind, sham-controlled, crossover randomised multicentre study in 25 adults with OCD. Each participant will receive three courses of tDCS (SMA, OFC and sham), randomly allocated and given in counterbalanced order. Each course comprises four 20-min stimulations, delivered over two consecutive days, separated by at least 4 weeks’ washout period. We will collect information about recruitment, study conduct and tDCS delivery. Blinded raters will assess clinical outcomes before, during and up to 4 weeks after stimulation using validated scales. We will include relevant objective neurocognitive tasks, testing cognitive flexibility, motor disinhibition, cooperation and habit learning.

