### Sample size calculation

Study sample size is evaluated with respect to the primary outcome (difference in the challenge Y-BOCS between tDCS and Sham), given that the aim is to estimate the likely effect size of a future trial. We assume that the sample will be representative of the population, and that the observed variance, and Y-BOCS scores in each condition will allow for estimation of a typical group comparison. Given that there are only 4 exposures of tDCS in each study condition, with 4 weeks between exposures, we assume no carry-over effects, which will be tested using a mixed model. Each tDCS target (OFC and SMA) will be considered independently against Sham. Published estimates of effect size vary widely [45]; thus, a conservative estimate of *d* = .3 is assumed. Following Cocks and Torgersen [51], assuming *α* = 0.05, 1 – *β* = 0.80, a sample size of 20 per group allows detection of a lower limit of *d*’ > 0.1 for an expected effect size *d*’ = 0.3. An additional 5 patients will allow for a 25% dropout.

It is estimated that approximately 25 patients will be recruited from a pool of 200 patients identified from screening, giving power to estimate the ascertainment ratio to within ± 6%. The proportion of missed treatment sessions is expected to be less than 20% from a total of 206 sessions, giving a precision within ± 6%. At the outset of the study, it is not possible to estimate the likely number of reported adverse events (safety), which is expected to be low, and cannot therefore estimate the likely precision of estimation.

Time-dependent changes in the Y-BOCS scores, and in the CANTAB test scores will be considered using standard paired comparisons (*t* test). A sample size of *N* = 20 allows for detection of an effect size *d*’ = .65 with power 1 – *β* = .78, and an effect size *d*’ = .77 with power 1 – *β* = .90. A time-dependent model will be evaluated (mixed model) to examine trends over time, but with limited power.

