#### Feasibility of recruitment

The flow of patients through the study, from identification to randomisation, to completion of the study outcomes will be logged, allowing the ascertainment ratio to be estimated. The proportions of patients agreeing to be screened and randomised will be described. The reasons for refusal to take part will be documented and listed. It is expected that approximately 200 patients will be screened to recruit to target, such that proportions can be estimated to within ± 10%.

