#### Adherence to tDCS and study assessments

Adherence will be evaluated by estimating the proportion, and range of sessions completed. The total number of sessions per patient will be 12, giving a limited power to evaluate differences between treatment conditions, but where comparison is possible, relevant analysis will be undertaken.There are a range of study assessments that will be completed. The number of missing assessments or responses will be estimated for each patient, and comparison by treatment intervention will be evaluated using the McNemar test.Reasons for non-completion will be recorded and listed by treatment intervention allowing comparison between the treatments.

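### The planning figures for sessions, ascertainment and dropout conflict with the design, and the ±6% precision for missed sessions ignores that sessions are nested within patients

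*Protocol article*

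**What the plan says.** All places are in the Protocol article.

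- **Sessions.** The abstract's Methods gives three courses, and "Each course comprises four 20-min stimulations, delivered over two consecutive days". The section Adherence to tDCS and study assessments agrees: "The total number of sessions per patient will be 12". Sample size calculation nevertheless describes missed sessions as "expected to be less than 20% from a total of 206 sessions". It puts the precision of that proportion at ±6%.
- **Ascertainment.** Sample size calculation assumes that "approximately 25 patients will be recruited from a pool of 200 patients identified from screening". From this it claims ±6% for the ascertainment ratio. Recruitment gives limits of ±10% for the same ratio. Feasibility of recruitment also uses ±10%, on about 200 screened ("such that proportions can be estimated to within" that margin).
- **Dropout.** Sample size calculation needs 20 evaluable patients and adds: "An additional 5 patients will allow for a 25% dropout".
- **Analysis.** Statistical analysis describes the feasibility analysis as descriptive. No confidence level accompanies any of the precision figures.

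**The concern.** Recruitment and adherence are among the main feasibility objectives, and these sentences tell the reader how well each will be estimated. The session denominator cannot be obtained from the design. The session precision is what independent observations would give, but each patient contributes 12 sessions and one who withdraws forfeits all the later ones, so misses will come in blocks. Withdrawal criteria has willingness reconfirmed at the start of each round, and the sample size itself allows for dropout, so this is foreseen.

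At stake is an adherence estimate that a full-scale trial would take over as firmer than it is. The other two items matter less. Two precisions for one ratio leave the reader unsure which was planned, and the dropout wording implies 20 evaluable patients at a loss rate that would leave fewer.

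**Working it through.** **Inputs from the protocol:** 12 sessions per patient; 25 enrolled, 20 evaluable; six sequences of 4, i.e. 24 (Randomisation scheme); 206 sessions; 20% missed; 25 recruited of 200.

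**Assumptions, not in the protocol:** 95% confidence; the within-patient correlation ρ; the timing of withdrawal.

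**1. Session total**
- 25 × 12 = 300; 24 × 12 = 288; 20 × 12 = 240.
- 206 / 12 = 17.2, which is not a whole number of patients.

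**2. Reproducing the ±6%**
- Half-width = 1.96 × √(p(1 − p)/n).
- p = 0.20, n = 206: 1.96 × √(0.16/206) = 5.5 points, so ±6% follows as a bound if all sessions are independent.
- On the same basis, n = 240 gives 5.1 points and n = 300 gives 4.5.

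**3. Allowing for 12 sessions per patient**
- Design effect = 1 + (12 − 1)ρ. Half-width = 1.96 × √(0.16 × design effect / 300).

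| ρ (assumed) | Design effect | Half-width, 25 × 12 sessions |
|---|---|---|
| 0.05 | 1.55 | ±5.6 points |
| 0.1 | 2.1 | ±6.6 |
| 0.2 | 3.2 | ±8.1 |
| 0.3 | 4.3 | ±9.4 |
| 0.5 | 6.5 | ±11.5 |

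- Break-even: ±6 points needs 0.16 × (1.96/0.06)² ≈ 171 effective sessions. With 300 sessions the largest tolerable design effect is 300/170.7 = 1.757, so ρ = 0.757/11 ≈ 0.07. The same step gives about 0.04 for 240 sessions and 0.02 for 206.

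**4. A check without an assumed ρ**
- Let 20% of the 25 patients withdraw, half after course 1 (missing 8/12 = 2/3) and half after course 2 (missing 4/12 = 1/3), with no other misses.
- Mean missed = 0.1 × 2/3 + 0.1 × 1/3 = 0.10.
- Between-patient variance = 0.1 × 4/9 + 0.1 × 1/9 − 0.10² = 0.0456.
- Half-width = 1.96 × √(0.0456/25) = 8.4 points.
- Independent sessions at the same 10% would give 1.96 × √(0.09/300) = 3.4 points.

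**5. Ascertainment**
- 25/200 = 12.5%; 1.96 × √(0.125 × 0.875/200) = 4.6 points (Wilson interval 8.6% to 17.8%).
- The largest half-width for any proportion of 200 is 1.96 × √(0.25/200) = 6.9 points.
- Both ±6% and ±10% are therefore true bounds for this ratio, but they differ from each other.

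**6. Dropout**
- 5/25 = 20%. The stated 25% is 5/20, the loss expressed against completers.
- 25 × 0.75 = 18.75, so 18 to 19 remain. Covering 25% would need 20/0.75 = 26.7, i.e. 27.
- Two-sided paired t test at d = 0.65: power 0.79 with 20 patients (the protocol states .78), 0.76 with 19 and 0.74 with 18.

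**The case against.** A reader might infer that all these errors make the feasibility estimates look more precise than they are. The figures do not support that. Replacing 206 by 300 narrows the unclustered interval from ±5.5 to ±4.5 points. Both ascertainment bounds are wider than the computed ±4.6, and within-patient clustering does not touch that ratio, since each screened patient counts once. The dropout wording bears on evaluable numbers, not on the feasibility proportions. This objection stands, and it confines the overstatement to missed sessions.

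A reader might also infer that the adherence interval will be far too narrow when analysed. The protocol plans no session-level interval: the feasibility analysis is descriptive, adherence is a proportion and range, and the interval method may sit in an analysis plan that is not shown. That stands too. The fault is in the stated planning precision.

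The correlation is assumed, and at 0.05 with 300 sessions the ±6% still holds. This is fair, and it is why no single clustered figure should be written into the protocol as fact. It does not rescue the ±6%, because the withdrawal check breaks it with no chosen correlation and with a loss inside the protocol's own allowance.

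Finally, little hangs on these numbers. The progression section sets no missed-session threshold, and the ascertainment target of 10% is not tied to a confidence limit. Dividing 5 by 20 is a common shorthand, the shortfall is one or two patients, and the planned mixed models can use partial completers. These points limit the weight of the matter but leave the contradictions in place.

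**Conclusion.** The point holds as a set of corrections, one of them substantive.

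- **Missed-session precision: overstated.** At 20% missed, ±6% needs a within-patient correlation of no more than about 0.07 with 300 sessions. Over an assumed range of 0.05 to 0.5 the half-width is ±5.6 to ±11.5 points. Withdrawal of 20% alone gives about ±8.4, assuming an even split after course 1 or 2.
- **206 sessions: contradicts the design.** It should be 300, 288 or 240, depending on the patients counted. Taken alone, the error is conservative.
- **Ascertainment: inconsistent, not false.** ±10% and ±6% are both valid loose bounds; the 95% figure for 25/200 is about ±4.6 points. The firm conflict is between Recruitment and Sample size calculation, because the ±10% in Feasibility of recruitment refers to proportions more generally.
- **Dropout: mislabelled.** The allowance is 20%. A true 25% loss leaves 18 to 19, below the N = 20 behind the stated power.

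The half-widths are normal approximations at an assumed 95% level.

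**What to change.** 1. Sample size calculation: replace 206 by 300 planned sessions for 25 patients (288 if 24 are randomised, 240 for 20 completers).
2. Same section: restate the missed-session precision with the patient as the unit, naming the correlation or withdrawal pattern assumed and, preferably, showing a range. Report the adherence proportion with a patient-level or cluster-robust interval, such as a bootstrap over patients.
3. Recruitment, Sample size calculation and Feasibility of recruitment: give one precision for the ascertainment ratio with its confidence level, for example 12.5% ± 4.6 points at 95%. If ±10% is kept for other recruitment proportions, say which ones.
4. Sample size calculation: describe the 5 extra patients as covering 20% dropout.

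The cost is rewording and one cluster-aware interval. Enrolment need not change. The stated adherence precision will probably become less favourable, and the ascertainment precision slightly more so.

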## Method/design

### Aim

#### Primary objective

The main aim of this feasibility trial will be to inform the development of a subsequent definitive tDCS full-scale trial. This feasibility trial will collect information about recruitment, study conduct, tDCS delivery, and assessment methods to inform future trial design.

The objectives of this feasibility trial will be to assess:

•Acceptability and safety of the intervention

•Feasibility of recruitment

•Adherence and tolerability of tDCS and study assessments

•Willingness of clinicians to recruit participants

•Practicality of applying tDCS in the clinical setting

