### Statistical analysis

The study is designed to evaluate the feasibility of delivering a crossover randomised trial of the tDCS treatment intervention, with a limited sample size. The primary aims described above are focused on the feasibility of delivering the trial, and the associated analysis will be descriptive. The secondary analysis considers the clinical and neuropsychological outcomes, and will consider the potential effect size of the intervention, change in clinical effect over time, and the effect of the tDCS intervention on neuropsychological status.

The analysis will consider:

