#### Acceptability, tolerability and safety

Treatment logs will be maintained, and the number of completed, shortened and missed sessions will be summarised by treatment condition. Reasons for refusal to complete or missing a treatment session will be recorded and tabulated. Comparison between treatment conditions will be evaluated using a McNemar test.Incidents related to safety and tolerability will be logged during the exposure to tDCS and in the following weeks. The nature of the adverse events will be documented, classified (as outlined in the “Measures” section) and listed. The number of scope of the events in each of the study conditions will be compared using a McNemar test.

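### The protocol says safety precision cannot be estimated, though the sample size already gives it, and it compares adverse events only by a McNemar test that says little at low event rates

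*Protocol article*

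**What the plan says.** The Primary objective section of the protocol article lists "Acceptability and safety of the intervention" first among the things to be assessed. The Sample size calculation says that the likely number of adverse events is not known at the outset, and continues "which is expected to be low, and cannot therefore estimate the likely precision of estimation". The sentence before that one gives a precision for missed sessions, within ± 6%, from an assumed rate below 20% and 206 sessions.

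Under Acceptability, tolerability and safety, events are logged, classified and listed. Then "The number of scope of the events in each of the study conditions will be compared using a McNemar test". This is the only comparison of events between conditions that the section names. The Statistical analysis section says of the primary aims that "the associated analysis will be descriptive".

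**The concern.** The Sample size calculation treats an unknown, low event rate as a reason why no precision can be given. A low rate is where a zero-event upper limit is most useful, and that limit needs only the number of patients.

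With precision set aside, the comparison named for safety is a significance test. A test on about 20 to 25 pairs with few events will usually be non-significant whether or not a moderate excess exists. A team planning the full trial needs to know how large an event rate, or an excess over sham, the data still allow. A p-value does not tell them.

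**Working it through.** **Inputs from the protocol article**
- 25 patients planned, each receiving all three conditions (Abstract, Methods).
- 20 after the allowance in the Sample size calculation: "An additional 5 patients will allow for a 25% dropout".
- Missed sessions: rate below 20%, 206 sessions, ± 6% (same section).

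**Assumptions**
- Each patient counts once per condition, as having the event or not. McNemar's test needs this.
- Two-sided 0.05 for the McNemar test. The protocol states 0.05 for the Y-BOCS effect size and no level for this test.
- Event rates are not given beyond being low, so a range is used.

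**Step 1: the plan's own precision figure.** The 95% half-width is 1.96 × √(p(1 − p)/n). With p = 0.20 and n = 206 this is 1.96 × √(0.16/206) = 5.5%, which agrees with the stated ± 6%. An assumed rate was enough here.

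**Step 2: the same for safety, per condition.**
- Zero events, one-sided 95% upper limit, 1 − 0.05^(1/n): n = 25 gives 11.3%; n = 20 gives 13.9%.
- Zero events, two-sided 95% Clopper-Pearson upper limit: 13.7% (n = 25), 16.8% (n = 20).
- Two-sided 95% Clopper-Pearson intervals: 1/25 gives 0.1% to 20.4%; 2/25 gives 1.0% to 26.0%; 5/25 gives 6.8% to 40.7%.
- Worst case, p = 0.5: 1.96 × √(0.25/25) = 20 points; 1.96 × √(0.25/20) = 22 points.

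**Step 3: what the McNemar test can show.** Only discordant patients count. If all D discordant patients point the same way, the exact two-sided p is 2 × 0.5^D. D = 5 gives 0.0625 and D = 6 gives 0.031, so at least 6 are needed, and 6 suffice only if all are in one direction. The uncorrected chi-square is (b − c)²/(b + c). For 4 against 0 it is 4 (p = 0.046), and for 3 against 0 it is 3 (p = 0.083), so 4 are enough.

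If the sham rate is 0%, every event is discordant and the discordant count is binomial(n, active rate). The chance of missing the difference is then P(count < 6) for the exact test and P(count < 4) for the uncorrected one:

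| Active v sham | Exact, n = 20 / 25 | Uncorrected, n = 20 / 25 |
|---|---|---|
| 10% v 0% | 99% / 97% | 87% / 76% |
| 20% v 0% | 80% / 62% | 41% / 23% |
| 30% v 0% | 42% / 19% | 11% / 3% |

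With a non-zero sham rate and independent responses within a patient, by full enumeration:

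| Active v sham | Exact, n = 20 / 25 | Uncorrected, n = 20 / 25 |
|---|---|---|
| 20% v 10% | 96% / 93% | 87% / 85% |
| 25% v 5% | 80% / 68% | 58% / 50% |

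A 10-point excess was missed at least 76% of the time in every variant computed, including mid-p and maximal within-patient correlation.

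**The case against.** The strongest reply is that this is a feasibility study which does not claim to infer safety. The analysis of the primary aims is called descriptive, events are listed with severity and relatedness, and clinician reviews and Trial Steering Committee oversight deal with safety as the study runs. No item among the principal data under Progression to a full trial depends on the McNemar result. All of this stands. A reader might infer that the protocol will take a null result as evidence of safety, but no section says so.

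A reader might also infer that an excess of 1 in 5 patients would usually be missed. For 20% v 0% this is true of the exact test, but the protocol does not name a version, and the uncorrected chi-square misses that difference only 41% (n = 20) or 23% (n = 25) of the time. An excess of about 30 points over a near-zero sham rate could well be detected.

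The wording on precision can also be read kindly: the expected width of an interval does depend on the event rate. But a zero-event limit, a worst-case half-width or a short table over assumed rates was available, and the adjacent sentence takes the assumed-rate route for missed sessions.

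Finally, intervals may be left to an analysis plan that is not shown. Their absence is not the point here. The point is a stated reason that is wrong and a comparison that is fixed in the text and suits the expected data poorly.

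**Conclusion.** The concern holds in a limited form. The statement that safety precision cannot be estimated is wrong: zero events in 25 (20) patients gives a one-sided 95% upper limit of 11.3% (13.9%), with no assumption about the rate. The McNemar test, as the only named comparison between conditions, carries little information at the low rates the protocol expects. For 10% v 0% the exact version misses 97-99% and the uncorrected version 76-87%.

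The precision figures rest on counting patients once per condition. The miss rates also rest on assumed event rates and a two-sided 0.05 level, since the documents give no rates and define no harm of interest. The conclusion does not extend to large excesses, nor to a claim that the protocol equates non-significance with safety. The latter is a risk of interpretation, and one sentence would close it.

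**What to change.** In the Sample size calculation, replace the sentence on safety with the precision the design gives. For example: with 25 (20) patients per condition, zero events gives a one-sided 95% upper limit of 11.3% (13.9%) for the proportion of patients affected. A short table over assumed rates would serve as well.

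Under Acceptability, tolerability and safety, keep the listing and base the comparison on:
- the number of patients with at least one event in each condition, with exact 95% limits;
- the OFC-sham and SMA-sham paired risk differences, with 95% intervals.

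Make any McNemar p-value secondary, and state that non-significance will not be taken as evidence of safety.

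This needs no new data, patients or visits. It costs some wording and a few lines of analysis. The downside is a safety statement that is visibly less reassuring, because the limits will be wide.

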### Statistical analysis

The study is designed to evaluate the feasibility of delivering a crossover randomised trial of the tDCS treatment intervention, with a limited sample size. The primary aims described above are focused on the feasibility of delivering the trial, and the associated analysis will be descriptive. The secondary analysis considers the clinical and neuropsychological outcomes, and will consider the potential effect size of the intervention, change in clinical effect over time, and the effect of the tDCS intervention on neuropsychological status.

The analysis will consider:

#### Acceptability, tolerability and safety

Treatment logs will be maintained, and the number of completed, shortened and missed sessions will be summarised by treatment condition. Reasons for refusal to complete or missing a treatment session will be recorded and tabulated. Comparison between treatment conditions will be evaluated using a McNemar test.Incidents related to safety and tolerability will be logged during the exposure to tDCS and in the following weeks. The nature of the adverse events will be documented, classified (as outlined in the “Measures” section) and listed. The number of scope of the events in each of the study conditions will be compared using a McNemar test.

#### Feasibility of recruitment

The flow of patients through the study, from identification to randomisation, to completion of the study outcomes will be logged, allowing the ascertainment ratio to be estimated. The proportions of patients agreeing to be screened and randomised will be described. The reasons for refusal to take part will be documented and listed. It is expected that approximately 200 patients will be screened to recruit to target, such that proportions can be estimated to within ± 10%.

#### Adherence to tDCS and study assessments

Adherence will be evaluated by estimating the proportion, and range of sessions completed. The total number of sessions per patient will be 12, giving a limited power to evaluate differences between treatment conditions, but where comparison is possible, relevant analysis will be undertaken.There are a range of study assessments that will be completed. The number of missing assessments or responses will be estimated for each patient, and comparison by treatment intervention will be evaluated using the McNemar test.Reasons for non-completion will be recorded and listed by treatment intervention allowing comparison between the treatments.

